#### Qualitative analysis

Interviews will be audio-recorded and transcribed using MAXQDA software (version 12.0 or later, VERBI, Berlin, Germany). Using a qualitative content analysis approach by Mayring, the transcribed data will be analyzed [31]. The evaluation process will be conducted in accordance with the Medical Research Council’s 2006 guidelines [44].

### Interim analyses {21b}

Not applicable.

### Methods for additional analyses (e.g., subgroup analyses) {20b}

Quantitative outcomes within subgroups will be analyzed using multivariate linear and logistic regression models. If differences between the intervention and control groups are observed at baseline, adjustments will be made for relevant covariates such as age, gender, and dementia severity. In addition to intention-to-treat analyses, per-protocol analyses will be conducted with participants who actually received the intervention. Further analyses will focus on specific subgroups of the study population, for example based on dementia severity or variations in home care settings.

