### Sample size {14}

Sample size was exclusively calculated based on a dichotomized threshold (≥ 12 months) of the PTS. Based on data from previous studies, 60% of informal caregivers of community-dwelling PlwD initially expressed their confidence in maintaining the informal care provision and the current care arrangements for at least 12 months. However, 10.5% of patients died and only 23% of the initial sample maintained this view one year later [21]. We, therefore, hypothesize that the intervention will increase this proportion to 35%, corresponding to an effect size of 0.25. Assuming a 1:1 randomization, statistical power of 80%, and a significance level of *α* = 0.05, a sample size of 224 dyads per group is required to detect a statistically significant effect based on a chi^2^ test. Considering an additional drop-out rate of 17.5%, summing up to 28% including death (in line with previously conducted study [43]), the target sample size increases to 272 dyads per group, resulting in a total of 544 dyads (1088 participants: 544 PlwD and 544 caregivers).

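### The stated subgroup method fits regressions within subgroups and names no treatment-by-subgroup interaction, so it cannot show whether the effect differs between subgroups

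*Protocol article*

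**What the plan says.** The method is in the protocol article under Methods for additional analyses {20b}: "Quantitative outcomes within subgroups will be analyzed using multivariate linear and logistic regression models". The same section closes with: "Further analyses will focus on specific subgroups of the study population, for example based on dementia severity or variations in home care settings". The subgroups are examples only; the article gives no number, cut-points or sizes.

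Statistical methods for primary and secondary outcomes {20a} sets the main models. These are a proportional odds model for the six-category Perseverance Time Scale (PTS), and linear and logistic models with a random effect for memory clinic for the secondary outcomes. The base case is intention-to-treat. Neither section mentions an interaction term, a heterogeneity test, or a rule for interpreting subgroup results.

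Power is given for one quantity only. Under Sample size {14}: "Sample size was exclusively calculated based on a dichotomized threshold" of the PTS, at 12 months or more.

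**The concern.** Whether an effect differs between subgroups is a question about the difference between two effects. Models fitted separately in each stratum estimate the two effects but not their difference, and give it no confidence interval. Each stratum also has fewer dyads than the trial was sized for. One stratum crossing 0.05 while the other misses it is therefore an ordinary result even when the true effect is the same in both.

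The Discussion says that positive results are to support moving the intervention into standard care. Dementia severity and home care setting are characteristics by which access could be limited. A mistaken report that the intervention helps only one kind of dyad could misdirect such a decision.

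**Working it through.** **Inputs from Sample size {14}.** Control proportion 0.23 ("only 23% of the initial sample maintained this view one year later"), intervention proportion 0.35, power 80%, 1:1 allocation, α = 0.05. Sidedness is not stated; two-sided reproduces the published number.

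**Assumptions.** Two subgroups, the same true effect in both, each tested at two-sided 0.05. Subgroup sizes are not given, so a range is shown.

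**1. The plan's own figure.** With pooled variance, mean proportion 0.29 and no continuity correction:

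n = [1.960·√(2·0.29·0.71) + 0.842·√(0.23·0.77 + 0.35·0.65)]² / 0.12² = (1.258 + 0.535)² / 0.0144 ≈ 223.3, so 224 per group. This matches the article. Its inflation for 17.5% drop-out also matches: 224/0.825 = 271.5, so 272.

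**2. Power in one half.** With 112 per arm:

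Φ[(0.12·√112 − 1.258)/0.636] = Φ(0.019) = 50.8%.

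**3. Exactly one of two significant.** With stratum powers a and b this is a(1 − b) + b(1 − a). For equal halves: 2 × 0.508 × 0.492 = 50.0%. Both are significant in 25.8% and neither in 24.2%. A simulation of 200,000 trials gave 50.1%.

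**4. Unequal splits, 224 per group.**

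| Split | Power, larger | Power, smaller | Exactly one significant |
|---|---|---|---|
| 60:40 | 58.3% | 42.4% | 51% |
| 67:33 | 62.9% | 36.4% | 54% |
| 75:25 | 68.0% | 28.6% | 58% |
| 80:20 | 70.8% | 23.7% | 61% |

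Over splits from 50:50 to 80:20 the range is 48% to 63% with 272 analysed per group, and 50% to 59% with 196 (272 less 28%).

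**5. Other overall power, equal halves.** Stratum power is Φ[(1.960 + z)/√2 − 1.960], where z is the normal quantile of the overall power. Exactly one half is significant in 29% of trials at 30% overall power, 41% at 50%, 50% at 80%, 47% at 90% and 40% at 95%. With no effect at all it is 2 × 0.05 × 0.95 = 9.5%.

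**6. The alternative.** In the same simulation (23% against 35% in both halves), a Wald interaction test on the log-odds scale at two-sided 0.05 declared a difference in 4.9% of trials.

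**7. Its price.** With equal halves, the standard error of the difference between the two subgroup effects is about twice that of the overall effect. An interaction as large as the whole design effect therefore has power of about Φ(2.802/2 − 1.960) = Φ(−0.559) ≈ 29%.

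**The case against.** The strongest reply is that this is silence rather than error. The section does not exclude an interaction term, the article condenses a fuller protocol, and a statistical analysis plan that is not shown may supply one. A reader might infer that the plan rejects interaction testing; the text does not support that. What stands is that the article does commit to a method, regression within subgroups, and that this method does not answer whether effects differ. Replacing it corrects a stated choice.

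A second reply is that 50% is only the chance of a split pattern of significance. A reader might infer that a uniform effect will be reported as subgroup-specific half the time. That would need a team or audience that treats such a split as effect modification, and no section says they will. This stands, so the claim is conditional. The number and sizes of subgroups are assumed, and the 80% power belongs to the dichotomised PTS used for sizing. The ordinal primary analysis and the other outcomes may give different figures.

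A reader might also infer that the ordinal primary outcome would be modelled differently in subgroups, because {20b} names only linear and logistic models. This is not established: logistic regression there can include the ordinal logistic model named in {20a}. Naming the model would remove the ambiguity.

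Nor should the false-positive risk of four within-stratum tests (1 − 0.95⁴ = 18.5% if independent) be set against 5% for one interaction test. Over two factors the comparable figure is 1 − 0.95² ≈ 9.8%. The four tests are also not independent, and the two rates count different errors.

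Finally, these are additional analyses, and the Discussion does not tie adoption to subgroup results. That limits the weight of the point but does not remove it.

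**Conclusion.** The point holds in a limited form. The only subgroup method in the article analyses outcomes within subgroups, and that cannot show whether the effect varies by dementia severity or home care setting. If significance is compared across strata, a uniform effect could appear confined to one of two equal subgroups in about 50% of trials at the design effect, against about 5% for an interaction test. Under the sensitivity ranges shown, the misleading pattern remains common whenever there is a real effect.

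The size rests on two subgroups, equal true effects, the dichotomised PTS, and a reader who contrasts significant with non-significant strata. The primary analysis is untouched. The change is worth making because it is cheap and the subgroup results could be used when adoption is discussed.

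**What to change.** Replace the within-subgroup sentence in {20b} with wording to this effect:

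- Subgroup effects are assessed in the full intention-to-treat sample by adding a treatment-by-subgroup interaction to the main-analysis model for each outcome, stated explicitly as the proportional odds model for the PTS.
- Subgroups are formed from baseline values only.
- The interaction estimate is reported with its 95% confidence interval.
- Stratum effects are shown descriptively.
- The analysis is labelled exploratory.

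The cost is one sentence and, for a two-level factor, one extra model term, with no additional data or participants. Recruitment is expected to run until July 2027 with follow-up 12 months after baseline, so the change can be made before outcome data are complete. The downside is low interaction power: a non-significant interaction will not show that the effect is uniform, and fewer subgroup results will be significant.

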### Trial design {8}

The *living@home* study is a multi-center, randomized, controlled intervention study with two parallel arms: an intervention arm and a control arm (care as usual). Dyads in the intervention group will receive an individualized dementia care management for a period of 12 months, aiming to identify and effectively address the unmet needs of PlwD and their caregivers. The intervention will be supported by a mobile health app used by both caregivers and Care Specialists, enabling caregivers to access care managers and memory clinics at any time when needs or burdens are faced. Therefore, the app will be used to monitor the caregiver’s health situation and burden through regular real-time data collection, aggregation, and transmission to the care manager for timely interventions or re-interventions tailored to the individual caregiver’s burden. The core items and their respective cut-offs are summarized in Table 1.

**Table 1 Tab1:** App-based monitoring and stratifaction

Item	Source/reference	Cut-off/threshold	Contact with family caregiver	Reassessment frequency
High caregiver distress	PTS and ZBI-12 and ZBI-1	PTS < 6 months or ZBI-12 ≥ 20 or ZBI-1 “extremelx”	Weekly intervention contact	Monthly
Moderate caregiver distress		PTS < 6 and > 24 months or ZBI-12 < 20 or ZBI-1 “quite a bit”	Monthly intervention contact	Monthly
Low caregiver distress		PTS < 24 months or ZBI-12 < 10 or ZBI-1 “not at all/little/moderately”	Quarterly intervention contact	Quarterly

Thus, the intervention frequency and intensity are individualized to the dyads’ needs and the reported burden. Dyads in the control group will receive care as usual. Both groups will be assessed at baseline and after 12 months. The study flowchart is illustrated in Fig. 1.

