## Interventions

### Explanation for the choice of comparators {6b}

Dyads in the control group will receive care as usual, reflecting the current standard of care in German memory clinics and subsequent outpatient treatment and care.

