The content, the frequency and intensity of the intervention tasks are adjusted according to the caregiver’s burden and the stability of the home care situation, meaning that the higher the burden or the lower the home care stability, the more frequent and intense the intervention will be. Dyads with a low caregiver burden (ZBI-12 < 10 or ZBI-1 “not at all/little/moderately”) and a stable home care arrangement (Perseverance Time Scale > 24 months) are considered as low strain and will be contacted by the Family Care Specialist on a quarterly basis to check on their needs. Dyads with a moderate to high caregiver burden (ZBI-12 10–19 or ZBI-1 “quite a bit”, and ZBI-12 ≥ 20 or ZBI-1 “extremely”) or a moderate to low care arrangement stability (Perseverance Time Scale < 24 months and > 6 months, and < 6 months) are considered as medium to high strain resulting in a monthly or weekly contact frequency, respectively.

Besides these regular contacts (executed via a visit at the home of the PlwD or the caregiver or a phone call or a video call via the mobile health app) the caregivers can reach out to the Family Care Specialists anytime to seek assistance or advice. 

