#### Mobile health app

An additional key component of the intervention is the mobile health application, which is available to all participating caregivers. The app is used to execute repeated short assessments of the stability of the care situation and the caregiver burden, based on which the dyads are stratified into three intervention intensity levels. This ensures that dyads with a higher caregiver burden or less stable care arrangement receive more intensive support from the caregivers. Also, the level of strain determines the recurrence of the app assessments: dyads in the low-strain group are re-assessed via the app quarterly, while dyads in the moderate and high-strain groups are re-assessed monthly. Besides the tool for repeated assessment, the mobile health app contains several functionalities, such as a chat feature for messaging between the caregiver and the Family Care Specialist, a caregiver diary to capture health and life events, a digital library containing educational materials provided as videos, information text with links that help to address existing unmet needs, and a regional location guide for dementia-related support services.

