#### Primary outcome

The primary dyadic outcome is the caregiver’s self-assessment of the stability of the home care arrangement (Perseverance Time Scale) [11, 21]. Crucial secondary supportive outcomes are the presence, type and severity of neuropsychiatric symptoms of the PlwD (Neuropsychiatric Inventory) [22] and the caregiver burden (Zarit Burden Interview) [23, 24]:i.For the Perseverance Time Scale, informal caregivers are asked (self-assessment) to estimate how long they believe they can continue to provide informal care and, thus, their current care situation. Response options are less than 1 week, less than 1 month, less than 6 months, less than 1 year, less than 2 years, and 2 years or more.ii.The caregivers will also report on the Neuropsychiatric Inventory via face-to-face interviews with a qualified study nurse, providing details about the presence and severity of neuropsychiatric symptoms, including depression, aggression, hallucinations and other behavioral symptoms of the PlwD.iii.The Zarit Burden Interview (12-item version) and ZBI-1 will be used to measure caregiver burden via a self-assessment, measuring physical and emotional strain, social restrictions, financial burden, and perceived effects on caregivers’ health. 

The primary outcome is the stability of the home-based care arrangement, measured by the Perseverance Time Scale which operationalizes the caregivers’ subjective self-estimation of their ability to sustain the current home-based care arrangement. While caregivers’ predictions about future care capacities may be uncertain due to the chronic and progressive nature of the disease, the Perseverance Time Scale is short, easily applicable and well-validated for use in this population. As demonstrated by previous studies with informal caregivers of PlwD, the Perseverance Time Scale showed significant correlations with other burden-related measures, such as the Caregiver Strain Index, the Self-related Burden Scale or the CarerQol-VAS [25]. Changes in caregiver-reported outcomes will be contextualized with concurrent events, such as functional decline of the PlwD, hospitalizations, falls, or other health-related incidents, allowing for a more comprehensive understanding of care dynamics over time.

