### Participant timeline {13}

Participant recruitment will take place from January 2026 to July 2027. After recruitment and baseline assessment, dyads will be randomized. Dyads of the control group will receive the intervention for a duration of 12 months. The frequency of the intervention (meaning interactions with the Family Care Specialist) will be determined individually based on the stratification into low-, medium-, or high-strain group. Twelve months after baseline, the dyads will receive a follow-up assessment. The last intervention will thus be carried out in July 2028.

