## Statistical methods

### Statistical methods for primary and secondary outcomes {20a}

All data analyses will be conducted using pseudonymized datasets. Initially, all outcome variables will be subject to descriptive statistical analyses. At baseline, the intervention and control groups will be compared regarding significant differences, serving as a randomization check. If notable differences are identified, all subsequent analyses will be adjusted for the respective factors. After completing the assessment, we will conduct a drop-out analysis using multivariate logistic regression to evaluate any systematic differences between included and excluded patients.

For the primary outcome, an ordinal logistic regression (proportional odds model) will be used to analyze the full six-category ordinal scale PTS. The intervention effect on the secondary outcomes will be evaluated using multivariate linear and logistic regression models, adjusted for age, sex, and living situation (alone vs. together with the caregiver), and including random effects for the respective memory clinic to account for clustering. The different study sites will be treated as clusters in these analyses. The analyses will be done on intention-to-treat (base case analysis) and per-protocol analyses (sensitivity analysis).

For the health-economic evaluation, the incremental cost-effectiveness ratio (ICER) will be calculated by comparing the additional cost per QALY gained through the intervention. Nonparametric bootstrapping resampling will be used to account for sample uncertainty in the ICER estimates. Various willingness-to-pay thresholds will be applied to determine probabilities of cost-effectiveness.

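### The per-protocol set is defined by receipt of the intervention, so it can exclude dyads from one arm only and loses the protection of randomisation

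*Protocol article*

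**What the plan says.** The section on statistical methods for primary and secondary outcomes {20a} sets the roles: "The analyses will be done on intention-to-treat (base case analysis) and per-protocol analyses (sensitivity analysis". The only description of the per-protocol set is in the section on additional analyses {20b}: "per-protocol analyses will be conducted with participants who actually received the intervention". It gives no level of exposure and no criterion for the control arm.

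On the control arm, the comparator section {6b} says: "Dyads in the control group will receive care as usual, reflecting the current standard of care in German memory clinics". The trial design section {8} agrees. The participant timeline {13} says the opposite: "Dyads of the control group will receive the intervention for a duration of 12 months".

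Three further statements bear on what receipt could mean:

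- Under Intervention design {11a}, "the higher the burden or the lower the home care stability, the more frequent and intense the intervention will be".
- The highest tier in Table 1 is triggered by "PTS < 6 months or ZBI-12 ≥ 20 or ZBI-1" at its top category. PTS is therefore one of three triggers joined by 'or'.
- Under Mobile health app, "The app is used to execute repeated short assessments of the stability of the care situation and the caregiver burden". Tiers are therefore updated during follow-up.

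PTS is also the endpoint: "The primary outcome is the stability of the home-based care arrangement, measured by the Perseverance Time Scale".

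**The concern.** A dyad allocated to care as usual has no study intervention to receive. Applied to a two-arm comparison, the stated rule keeps all controls and drops those intervention dyads that did not take up the programme. That is selection after randomisation in one arm only. If the dyads that do not take it up differ in prognosis from those that do, the two groups differ even when the intervention does nothing.

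Two plausible routes point in opposite directions:

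- **Overburdened caregivers may not engage.** The introduction itself says that caregiver workload hampers the use of support services. Dropping these dyads flatters the intervention.
- **Receipt might be judged by number of contacts.** Low-strain dyads, contacted quarterly by design, would then be the ones to fail the criterion, and dropping them penalises the intervention. Receipt would also depend on PTS, ZBI-12 or ZBI-1 as measured during the trial, because these set the contact frequency.

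At stake is whether agreement or disagreement between the per-protocol and intention-to-treat results tells the reader anything.

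**Working it through.** **Inputs from the sample size section {14}:** 23% of controls and 35% of intervention dyads with PTS of at least 12 months at one year; 80% power; alpha 0.05; 1:1 allocation; 224 per group before and 272 after 17.5% drop-out.

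**The plan's own figure.** Two-sided, no continuity correction, mean proportion 0.29:

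n = [1.960 × √(2 × 0.29 × 0.71) + 0.842 × √(0.23 × 0.77 + 0.35 × 0.65)]² / 0.12² = 223.3, rounded up to 224.

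224 / 0.825 = 271.5, rounded up to 272. Both figures reproduce, so the inputs are sound to build on.

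**Assumed inputs.** The protocol gives no rate of non-receipt. Let e be the fraction of the intervention arm excluded (10%, 20%, 30%). Let q be the proportion of those excluded who have PTS of at least 12 months (10%, 23%, 40%).

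**Bias with no true effect.** With 23% in both arms, the proportion among the intervention dyads kept is

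p_kept = (0.23 − e × q) / (1 − e),

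and the spurious difference is p_kept − 0.23 = e × (0.23 − q) / (1 − e).

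Example: e = 0.30 and q = 0.10 give (0.23 − 0.03) / 0.70 = 0.286, or +5.6 points. With q = 0.40 the result is (0.23 − 0.12) / 0.70 = 0.157, or −7.3 points.

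**False rejection rate.** Pooled two-proportion z-test, nominal 5% two-sided, 224 controls against 224 × (1 − e) intervention dyads.

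| PTS ≥ 12 months among excluded (q) | 10% excluded | 20% excluded | 30% excluded |
|---|---|---|---|
| 10% | +1.4 points, 6.4% | +3.3 points, 11.8% | +5.6 points, 23.6% |
| 23% | 0, 5.0% | 0, 5.0% | 0, 5.0% |
| 40% | −1.9 points, 7.5% | −4.3 points, 17.7% | −7.3 points, 41.4% |

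Each cell shows the spurious difference, then the rejection rate. The table uses the dichotomised PTS because the protocol gives planning figures only for that. It ignores covariates and clinic effects, and it is not the planned proportional odds model.

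**The same scenario with a complier-average effect.** If no control takes up the programme, this effect on the risk-difference scale is the intention-to-treat difference divided by the uptake fraction. With no true effect it is 0 / (1 − e) = 0 for every e and q in the table. At the planned 12 points and an assumed uptake of 80%, it is 12 / 0.80 = 15 points.

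**The case against.** **This is shorthand in a condensed article.** Read literally, the phrase would exclude every control and leave no comparison. Exposure thresholds and deviation criteria are usually set in an analysis plan, which is not shown. This stands as far as missing detail goes. It does not answer the point, because the article already states the selection principle, and that principle is one-sided. A precise threshold on receipt alone would still act in one arm only.

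**Any per-protocol comparison with usual care has this limit, and intention-to-treat is the base case.** Both are true, and they limit the weight of the point. They do not make the named sensitivity analysis interpretable.

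**The sizes rest on assumed inputs.** They do. The range runs through zero, and its ends depend on a prevalence that the protocol does not give.

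**Selection on contact intensity.** A reader might infer that the per-protocol set selects on an intensity set by the primary outcome itself. The protocol does not support that. The text selects on having received the intervention, not on number of contacts, and a low-strain dyad contacted quarterly has received it as planned. The dependence arises only if receipt is later defined by contact counts. Even then PTS is one of three triggers.

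**Conclusion.** The point holds as a minor one. As stated, the per-protocol criterion can exclude dyads only from the intervention arm, after randomisation, so the contrast is no longer a randomised one. Under the assumed exclusion of 10% to 30% and no true effect, the spurious difference lies between +5.6 and −7.3 points as the prevalence of PTS of at least 12 months among those excluded goes from 10% to 40%. It is zero if non-receipt is unrelated to outcome, but nothing in the stated rule secures that.

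Two stronger conclusions are not supported. The bias cannot be said to favour the intervention, because its direction is unknown. The primary conclusion is not at risk, because intention-to-treat is the base case. Per-protocol is also only the one analysis that this article labels as a sensitivity analysis; others may exist in documents not shown.

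The conclusion takes the control arm to receive care as usual, as the trial design and comparator sections say. The participant timeline contradicts this. While it does, the phrase about who received the intervention is harder still to apply.

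**What to change.** 1. Make the main adherence analysis a complier-average effect, for PTS of at least 12 months and for ZBI-12. Keep all randomised dyads in both arms, use randomisation as the instrument, and handle missing outcomes as in the intention-to-treat analysis.
2. Define take-up in advance and independently of strain tier, for example home-visit needs assessment done and task list started.
3. If a per-protocol analysis is kept, define adherence relative to each dyad's assigned tier, use deviation criteria that can apply in both arms, and label the result as a non-randomised comparison.
4. Reconcile the participant timeline {13} with the trial design {8} and comparator {6b} sections on which arm receives the intervention.

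The cost is one further model. The intervention management system already generates the task lists and supports intervention monitoring, so no new data collection should be needed. The downsides are a wider confidence interval and reliance on the exclusion restriction, that is, that allocation affects outcome only through take-up. The complier-average effect rescales the intention-to-treat effect and is not an independent check on it. On dichotomised PTS it also does not test the proportional odds model planned for the six-category scale.
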